### Premature closure of the study

Study participation by individual sites or the entire study may be prematurely terminated, if in the opinion of the sponsor, there is sufficient reasonable cause. Any investigator who wants to discontinue his/her participation to the study must immediately inform the sponsor in writing of this decision. Written notification documenting the reason for study termination will be provided to the investigator by the terminating party.

Examples of circumstances that may warrant termination include: failure to enter patients at an acceptable rate, insufficient adherence to protocol requirements, insufficient complete and/or evaluable data, frequency and/or unexpected severity of the toxicity, unacceptable toxicity. Each fatal event occurring within the 60th postoperative days will be immediately reported to the sponsor and to Data and Safety Monitoring Board (DSMB) members. The DSMB will be provided with the description of the fatal events to determine if the death has to be considered as a toxic one.

The statistical stopping rules are the following: for each toxic fatal event in the HIPEC arm, an analysis comparing the total number of patients included to the number of patients satisfying maximum toxic fatal event criteria will be performed to determine if the study should be stopped. This analysis will be realized with the Kramar sequential method
[43] as implemented in the R-package
[44]. This analysis will be performed using the following parameters: the maximum acceptable percentage of toxic deaths is fixed at 10% [the global alpha at 10%, and gamma at 4 (i.e., high alpha level at the beginning of the trial)], considering that the first toxic fatal event will not be taken into account.

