## Methods/design

### Protocol overview

GASTRICHIP is a prospective, open, randomized multicenter phase III clinical study aimed to evaluate the effects of HIPEC with oxaliplatin on patients with gastric cancer involving the serosa and/or lymph node involvement and/or with positive cytology at peritoneal washing, treated by D1-D2 curative gastrectomy (Figure 
1 – Flow chart study). Patients will be randomly assigned in a 1:1 ratio to: Arm A: curative gastrectomy with D1-D2 lymph node dissection + HIPEC with oxaliplatin versus Arm B: curative gastrectomy with D1-D2 lymph node dissection without HIPEC.

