### Sample size calculation and statistical considerations

This study is designed as a randomized phase III in order to compare the 5-year overall survival in patients with advanced gastric carcinoma randomized to hyperthermic intraperitoneal chemotherapy administration versus that of patients randomized to control arm.

The hypotheses are the following: 5-year overall survival in the control group of about 30%
[9,10]; 5-year overall survival in the intervention group of about 45% (i.e. an HR of 0.67)
[45]; a maximum follow-up time of 5 years; an alpha of 5%, two-sided. With this hypothesis and to have a 80% power, a total of 306 patients will have to be randomized. Since 5% of patients are expected to excluded during surgery (peritoneal carcinomatosis), a total of 322 patients will be included.

The effectiveness analysis will be carried out on the intention-to-treat population, defined as all patients included. A second analysis will be conducted on the “treated” population, determined according to the treatment actually administered (*per protocol* analysis). Overall survival will be measured from the date of surgery up to the date of death, regardless of the cause, or to the end of follow-up (5 years). The Kaplan-Meier method will be used to estimate the survival curves. Median survival will also be given and differences between the two groups assessed using a logrank test. This analysis will then be confirmed using a Cox regression analysis taking into account the center effect (frailty Cox model). The conditions for using the Cox regression analysis will be checked.

An intermediate analysis of toxicity will be realized at least every six months or every 50 patients randomized from the start of patients’ recruitment. The number of SAEs and AEs of severe (grade III-IV) with their accountability will be described.

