[51]. Recently, excellent results in treating colorectal peritoneal carcinomatosis have been reported for the use of HIPEC with oxaliplatin, with an exposure time of just 30 minutes. Furthermore, a French randomized, phase III study is currently assessing the use of HIPEC with oxaliplatin associated with complete cytoreductive surgery (CCS) to treat colorectal peritoneal carcinomatosis. These three studies used a dose of 460 mg/m^2^ of oxaliplatin for the open-abdomen technique and 350 mg/m^2^ for the closed-abdomen technique, administered in 2 liters/m^2^ of 5% glucose with the systemic administration of induction chemotherapy using FU/Leucovorin (400 mg/m^2^ 5-FU and 20 mg/m^2^ of folic acid) to increase the cytotoxic effect of the oxaliplatin. Glehen et al. recently published a report on the French experience in the curative treatment of gastric peritoneal carcinomatosis
[30]. The mortality rate was high, and reached 6%. This may be explained by the fact that the gastrectomy-HIPEC association increases the risk of severe postoperative complications. It would seem preferable to arbitrarily reduce the dose of oxaliplatin (250 mg/m^2^) in order to avoid an excessive rate of postoperative complications resulting from the experimental treatment.

The incidence of signet ring cell adenocarcinoma is steadily increasing in Western countries
[52,53]. Recent data has suggested not only that is has a negative prognostic value
[22], but that it is also chemo-resistant

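### The toxic-death stopping rule counts deaths in the HIPEC arm but names all patients included as the comparator; taken literally, its 10% limit works as about 20% in that arm

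*Protocol article*

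**What the plan says.** All statements are in the protocol article.

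- **Trigger and comparator** (Premature closure of the study). The rule is run "for each toxic fatal event in the HIPEC arm, an analysis comparing the total number of patients included to the number of patients satisfying" the maximum toxic-death criterion. It uses a published sequential method in its R implementation.
- **Parameters** (same section). "the maximum acceptable percentage of toxic deaths is fixed at 10" percent, with "the global alpha at 10%, and gamma at 4 (i.e., high alpha level at the beginning of the trial".
- **First death** (same section). The rule is applied "considering that the first toxic fatal event will not be taken into account".
- **Allocation** (Protocol overview). "Patients will be randomly assigned in a 1:1 ratio".
- **Size** (Sample size calculation and statistical considerations). "to have a 80% power, a total of 306 patients will have to be randomized". To allow for patients excluded during surgery, "a total of 322 patients will be included". The same section defines the intention-to-treat population as everyone included.
- **Other oversight**. Every death up to postoperative day 60 goes at once to the sponsor and the DSMB, and unacceptable toxicity is listed as a possible reason for closing the study. Toxicity is also reviewed at least every six months or every 50 randomised patients. No numerical threshold is attached to any of these.

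**The concern.** A sequential binomial rule works only if the deaths counted and the patients counted come from the same group. Here the deaths are those of one arm. The patient count carries no such restriction, and elsewhere in the article the same term covers both arms plus those never randomised.

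Whoever runs the boundary program must enter a patient count, and the printed sentence points to the larger one. That roughly halves the apparent toxic-death rate in the experimental arm. This is the only stopping criterion in the article with a number attached, so the DSMB could be told that the boundary has not been crossed when HIPEC-arm mortality is well above the stated maximum.

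The first-death clause adds a second uncertainty. It can mean that one isolated death never stops the trial, or that one death is permanently removed from the count. The two have different error rates.

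**Working it through.** **Inputs.** 306 randomised, 322 included, 1:1 allocation, maximum toxic-death rate p0 = 10%, global alpha 10%, gamma 4: all from the article. The form of the spending function is not given, so it is assumed below.

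**Step 1: the article's own sample size.** The article prints no boundary or stopping probability, so 306 is the figure to reproduce.
- HR = ln(0.45)/ln(0.30) = 0.663 (the article gives 0.67).
- Freedman events = (1.960 + 0.842)² × ((1 + 0.663)/(1 − 0.663))² ≈ 191.4, using the unrounded HR.
- Mean event share = (0.70 + 0.55)/2 = 0.625, and 191.4/0.625 ≈ 306. This agrees.
- 306 × 1.05 = 321.3, rounded up to 322. This agrees.
- HIPEC arm: 306/2 = 153.

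**Step 2: the effective limit.**
- 10% of 306 is 30.6 deaths; 30.6/153 = 20%.
- 10% of 322 is 32.2 deaths; 32.2/153 = 21%.

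**Step 3: the boundary.** Patients are added one at a time. After patient n of N, with t = n/N, the boundary is the smallest death count that keeps the cumulative false-stop probability at p0 = 10% within

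α(t) = 0.10 × (1 − e^(−4t)) / (1 − e^(−4)).

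This spends alpha early, as the article's remark on gamma requires.
- N = 153: alpha used 0.0998; final boundary 26 deaths, 26/153 = 17% of the HIPEC arm.
- N = 306: alpha used 0.0999; final boundary 45 deaths, 45/153 = 29% of the HIPEC arm.

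**Step 4: chance of stopping.** With a true HIPEC-arm rate p, the event probability per counted patient is p for N = 153, p/2 for N = 306, and p × 153/322 for N = 322. Exact recursion gives:

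| True HIPEC-arm rate | 153 HIPEC-arm patients | 306 randomised | 322 included |
|---|---|---|---|
| 10% | 10.0% | 0.19% | 0.15% |
| 15% | 57% | 1.6% | 1.1% |
| 20% | 94% | 10% | 7% |
| 25% | 99.8% | 39% | 31% |

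**Step 5: sensitivity to the spending form.** On 306 patients, at a true 15% and 20%, the rule stops in 0.8% and 10% of trials with gamma 1, and in 0.2% and 9% with gamma −4. On 153 HIPEC-arm patients the figures are 66% and 97%, and 72% and 98%. The loss does not depend on the assumed value.

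**Step 6: the first-death clause, on 153 HIPEC-arm patients.**
- No stop on a single death: the computed boundary is at least 2 from the first patient, so nothing changes.
- One death subtracted from the count (boundary raised by 1): stopping at a true 10% falls from 10% to 4%, at 15% from 57% to 43%, and at 20% from 94% to 90%.

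**The case against.** The best defence is that the sentence opens with the HIPEC arm, so the patients included may simply be those of that arm. It compares one number of patients with another, which suits a look-up table for a single-group rule. The article condenses a fuller protocol that may print that table, and the cited method is not shown. This stands in part: the sponsor may well have intended the HIPEC arm. The printed words do not say so, and the sample size section gives the term a trial-wide meaning.

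Four stronger readings are tempting, and the article does not support them.

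- **That a sound rule would stop at 10%.** With a global alpha of 10%, a correctly specified rule stops in only about 10% of trials at a true 10% rate, by design. The damage shows at rates above the limit.
- **That the literal rule cannot detect excess mortality.** It detects it rarely at 15% and 20%, but on 306 patients it stops in 39% of trials at 25% and 79% at 30%. The DSMB also sees each death within 60 days, and periodic toxicity reviews continue.
- **That the first-death clause in itself weakens the rule.** It does so only if the death is subtracted, which the text does not state.
- **That the 10% maximum contradicts the Discussion**, where "The mortality rate was high, and reached 6" percent. That figure comes from curative treatment of gastric peritoneal carcinomatosis, whereas macroscopic implants are an exclusion here. A ceiling for deaths judged toxic may also lie above a rate observed in another population without contradicting it.

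**Conclusion.** The concern holds as a mismatch in the printed rule: the deaths belong to one arm and the patient count, as worded, to the whole trial. Followed literally, the stated 10% limit acts as about 20% to 21% in the HIPEC arm. At a true rate of 20%, twice the stated maximum, the chance of stopping drops from 94% to between 7% and 10%.

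The size rests on the assumed exponential spending form, on each outcome being known at once (the 60-day window is ignored), and on treating 1:1 accrual as a constant fraction of the patients counted. The 20% figure in step 2 needs only the allocation ratio. Whether the rule would actually be run this way cannot be told from the article. The first-death clause is a secondary ambiguity, and the patient count drives the result.

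**What to change.** In Premature closure of the study:

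1. State that the boundary is computed on patients randomised to the HIPEC arm, so that the patient count matches the deaths counted and the stated 10% limit.
2. State that the first-death clause means that a single death does not stop the trial, and that this death stays in the count from the second death onward.

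The cost is a rewording and one rerun of the boundary program. If the larger count would otherwise have been used, DSMB review may be triggered earlier. The sample size and the efficacy analysis do not change.

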### Sample size calculation and statistical considerations

This study is designed as a randomized phase III in order to compare the 5-year overall survival in patients with advanced gastric carcinoma randomized to hyperthermic intraperitoneal chemotherapy administration versus that of patients randomized to control arm.

The hypotheses are the following: 5-year overall survival in the control group of about 30%
[9,10]; 5-year overall survival in the intervention group of about 45% (i.e. an HR of 0.67)
[45]; a maximum follow-up time of 5 years; an alpha of 5%, two-sided. With this hypothesis and to have a 80% power, a total of 306 patients will have to be randomized. Since 5% of patients are expected to excluded during surgery (peritoneal carcinomatosis), a total of 322 patients will be included.

The effectiveness analysis will be carried out on the intention-to-treat population, defined as all patients included. A second analysis will be conducted on the “treated” population, determined according to the treatment actually administered (*per protocol* analysis). Overall survival will be measured from the date of surgery up to the date of death, regardless of the cause, or to the end of follow-up (5 years). The Kaplan-Meier method will be used to estimate the survival curves. Median survival will also be given and differences between the two groups assessed using a logrank test. This analysis will then be confirmed using a Cox regression analysis taking into account the center effect (frailty Cox model). The conditions for using the Cox regression analysis will be checked.

An intermediate analysis of toxicity will be realized at least every six months or every 50 patients randomized from the start of patients’ recruitment. The number of SAEs and AEs of severe (grade III-IV) with their accountability will be described.

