### Surgical technique

At the opening of the abdomen, surgical exploration will be performed in order to compare data collected at preoperative videolaparoscopy with current operative findings including the effects coming from preoperative chemotherapy, namely the downstaging as far as T parameter is concerned, presence of serosal involvement and its extent, the absence of distant metastases and the feasibility of a D1-D2 resection with curative intent.

Peritoneal washing will then be performed: the abdomen will be irrigated with 200 ml of 0.9% NaCl solution (normal saline), left in the peritoneal cavity for 2 minutes and then all fluid will be aspirated from the four abdominopelvic quadrants [Left Upper Quadrant (LUQ) - Right Upper Quadrant (RUQ) - Left Lower Quadrant (LLQ) - Right Lower Quadrant (RLQ)]. All the collected fluid will be sent to the corresponding lab, where specimens for regular cytological analysis, cell blocks and immunohistochemistry (ancillary cytological study) will be sent to the Centre de Biologie et de Pathologie Est – Hospices Civils de Lyon.

All the patients will undergo a D1-D2 gastrectomy, carried out according to Japanese guidelines and to the European recommendations for the preservation of spleen and pancreas
[42]: lymphadenectomy will consist of removal of nodal groups 2 to 9 as specified by the JGCRS; group 1 will be added when total gastrectomy is performed and group 12 in distal cancers. *Ex vivo* separation of lymph node groups in individual containers before the surgical specimen is submitted to the pathologist is recommended. At the end of the gastrectomy procedure the peritoneal washing will be repeated with the same procedure.

Following randomization, the patients treated into the experimental Arm receive intravenous 5-FU 400 mg/m^2^ + calcium levofolinate 10 mg/m^2^) as systemic chemotherapy induction for HIPEC 15 min before HIPEC started. At the end of the procedure the patients in the experimental Arm will undergo HIPEC.

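### The second efficacy analysis groups patients by treatment received but is labelled per protocol; read literally it can count arm A patients not given HIPEC as controls, which favours HIPEC if non-receipt is linked to poor prognosis

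*Protocol article*

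**What the plan says.** In the protocol article, the section *Sample size calculation and statistical considerations* places the effectiveness analysis on the intention-to-treat population. It then announces a second analysis on a treated population, "determined according to the treatment actually administered", and names it per protocol in parentheses. It does not say how to classify an arm A patient who is not given HIPEC.

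Under *Protocol overview*, "Patients will be randomly assigned in a 1:1 ratio" to gastrectomy with or without HIPEC, in an open trial. The abstract puts randomisation during the operation, at the end of curative surgery. Under *Surgical technique*, intravenous induction is given after randomisation and 15 minutes before HIPEC, and "At the end of the procedure the patients in the experimental Arm will undergo HIPEC". Allocation and delivery are therefore separate steps with a short interval between them.

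**The concern.** A per-protocol analysis keeps the randomised arms and leaves out patients who departed from the protocol. An as-treated analysis ignores the allocation and regroups patients by what they received. The sentence gives the definition of the second and the name of the first, so two analysts could build different populations from it.

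The choice matters because departures are likely to be one-sided. The control arm is surgery without HIPEC, so nearly all non-receipt should fall in arm A. Under the literal rule those patients leave the HIPEC group and join the comparison group. If they are the patients with the worse outlook, the HIPEC group improves and the no-HIPEC group deteriorates without any treatment effect. A real effect would be exaggerated in the same way.

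**Working it through.** **The plan's own figure.** Inputs, all from *Sample size calculation and statistical considerations*: "5-year overall survival in the control group of about 30" per cent; "5-year overall survival in the intervention group of about 45% (i.e. an HR of 0.67"); "a maximum follow-up time of 5 years; an alpha of 5%, two-sided"; and "to have a 80% power, a total of 306 patients will have to be randomized".

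- HR = ln 0.45 / ln 0.30 = 0.663.
- Mean 5-year death probability = (0.70 + 0.55)/2 = 0.625.
- Freedman: events = (1.96 + 0.842)² × [(1 + 0.663)/(1 − 0.663)]² ≈ 191.4 (with the unrounded HR); N = 191.4/0.625 ≈ 306.
- Schoenfeld: 187 events; N = 187/0.625 = 299.2, so 300.

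The 306 is reproduced. The sample size is not in dispute, and 153 per arm is used below.

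**Assumptions not in the article.** A fraction f of patients in both arms would not receive HIPEC if allocated to it, and their death hazard is m times that of the others. Nobody in the control arm receives HIPEC.

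**Simulation.** Survival is exponential, with the base hazard set so that 30% of controls are alive at 5 years. Follow-up is censored at 5 years. Each scenario has 4,000 runs, analysed by log-rank test and Cox HR. Three populations are compared: as randomised (ITT); as-treated, with arm A non-recipients counted as controls; and per protocol, with arm A non-recipients dropped. Each cell gives the mean HR and the chance of a significant result for HIPEC when there is no effect (nominal 2.5%).

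| f | m | As-treated | Per protocol |
|---|---|---|---|
| 2% | 2 | 0.98, 3.6% | 0.99, 2.9% |
| 2% | 3 | 0.96, 4.9% | 0.98, 3.4% |
| 5% | 2 | 0.94, 6.3% | 0.97, 4.1% |
| 5% | 3 | 0.91, 9.7% | 0.95, 5.3% |
| 10% | 2 | 0.89, 13.5% | 0.94, 6.9% |
| 10% | 3 | 0.84, 23.2% | 0.91, 9.8% |

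ITT stays at HR 1.00 and about 2.5% throughout. With m = 1 all three populations give HR 1.00 and about the nominal rate.

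**Hand check of size and ratio.** Under as-treated grouping the HIPEC group holds none of the poor-prognosis patients. The no-HIPEC group holds 306f of them among 153(1 + f), a share of 2f/(1 + f). At f = 10% this is 30.6/168.3 = 18.2%. With m = 2 the HR at time zero is 1/(1 + 0.182) = 0.85. Dropping the patients instead leaves a share of f = 10% in control, so the starting HR is 1/1.10 = 0.91. Both move towards 1 over follow-up as the high-risk patients die, which agrees with 0.89 and 0.94. On the log scale, ln 0.937 / ln 0.887 = 0.54, so the per-protocol set carries about half the bias.

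**With a real effect.** If the true HR in recipients is 0.663, f = 10% and m = 2, as-treated gives 0.59, per protocol 0.62 and ITT 0.69.

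**The case against.** The strongest reply is that the article describes no mechanism. It does not mention patients too unstable for HIPEC, gives no reason for withholding it and states no rate. That is correct, and it rules out a reading that a reader might infer: that this analysis necessarily moves unstable patients into the control group and so favours HIPEC. The Discussion says that combining gastrectomy with HIPEC raises the risk of severe complications. That makes selective withholding plausible but does not document it.

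Late randomisation also limits the problem. Most of the operative course is known before allocation, so non-receipt may be rare, and at 2% with doubled hazard the distortion is small. The plan's own 5% does not help set the rate: "Since 5% of patients are expected to excluded during surgery (peritoneal carcinomatosis), a total of 322 patients will be included" concerns patients removed for carcinomatosis, not randomised patients who miss HIPEC.

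The label could also be taken to govern, so that non-recipients are dropped and nobody moves to control. This is a fair reading, but it contradicts the stated definition and reduces the bias without removing it. Finally, an article condenses a fuller protocol. That would excuse a missing rule; here a rule is stated, and it conflicts with its own name.

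**Conclusion.** The point holds as a defect in a secondary analysis: the definition is as-treated and the label is per protocol. If the definition is followed and non-receipt is linked to poor prognosis, the analysis is biased towards HIPEC. With doubled hazard and no true effect, the HR is about 0.98, 0.94 and 0.89, and the false pro-HIPEC rate about 4%, 6% and 14%, at 2%, 5% and 10% non-receipt. Both the rate and the hazard multiple are assumptions, and the bias is nil if non-receipt is unrelated to prognosis.

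Two further inferences are not supported. The article does not say that this analysis is meant to corroborate the primary result; it calls it only a second analysis, and the confirmatory wording in that section refers to the Cox model that follows the log-rank test. Nor is the primary conclusion at risk from this point, since the effectiveness analysis is by intention to treat. The change is worth making because it is cheap and removes a choice that would otherwise stay open once results are visible.

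**What to change.** Reword the sentence in *Sample size calculation and statistical considerations*, and any matching text in the analysis plan, before comparative outcome data are examined:

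- Keep patients in their randomised arm in every efficacy analysis.
- Define the per-protocol set as eligible randomised patients who received their allocated treatment, analysed as randomised.
- Label it supportive only, and state that it can still be biased towards HIPEC, by about half as much as the as-treated version (HR 0.94 against 0.89 at 10% non-receipt with doubled hazard).
- Report by arm the number of patients not given their allocated treatment and the reasons. These are the figures a reader needs to judge the bias.
- Use grouping by treatment received only for toxicity.

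A complier-average estimate respects randomisation and could be added, but it is optional. With censored survival it needs further assumptions, including about which control patients would not have received HIPEC.

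The cost is a change of wording and a slightly smaller supportive set. At 10% non-receipt, about 15 of the 153 arm A patients would be left out (0.10 × 153 = 15.3).

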### Peritoneal recurrence

Stomach cancer has the highest rate of peritoneal recurrence of all digestive cancers. After curative surgery, the main reason for treatment failure is peritoneal recurrence which, according to the literature, occurs in 40 to 60% of cases, despite extensive surgery including D2 lymph node dissection
[15,16].

Several factors favorable to peritoneal recurrence have been identified: invasion of the serosa (T3, T4 tumors)
[17,18], detection of free cancer cells in the peritoneal wash liquid
[19,20], invasion of the lymph nodes
[21], and signet ring cells adenocarcinoma
[22].

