### Main inclusion criteria

Patients 18 < age ≤ 75 years old with Karnofsky index ≥ 70% with histologically evidenced resectable T3 or T4 gastric adenocarcinoma for which a curative gastrectomy is scheduled, with invasion into the serosa and/or lymph node metastasis (determined from data obtained by endoscopic ultrasound and chest, abdomen and pelvis Computed Tomography (CT) scan) and/or positive peritoneal cytology (sampled during the preoperative laparoscopy) and/or perforated gastric adenocarcinoma and/or Siewert III adenocarcinoma of the cardia for which a gastrectomy by exclusive abdominal laparotomy is scheduled
[41].

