### Pre-therapeutic work-up

Patients eligible for the study will be seen in clinics following the explorative laparoscopy to check the inclusion and exclusion criteria. The patient will be required to give written informed consent to participate to this clinical study before any non routine screening tests or evaluations are conducted. Patients eligible for the study will be seen in clinics following the explorative laparoscopy to check the inclusion and exclusion criteria. The following assessments should be performed: Performance Status, upper intestinal endoscopy, endoscopic ultrasound, Thoraco-Abdomino-Pelvic CT scan, PET Scan (optional), laboratory exams: serum CEA, CA19.9 and CA72.4 (optional); hemoglobin, leukocytes, neutrophils, platelets, glycemia, AST, ALT, LDH, total bilirubin, alkalin phosphatase, serum albumin, total protein, plasmatic APTT, PT and INR; creatinine clearance and serum creatinine. Staging videolaparoscopy of the abdominal cavity and peritoneal cytology testing will be carried out following the same procedure as during gastrectomy. Patients with macroscopic peritoneal carcinomatosis not visible during the preoperative morphological examinations will be excluded from the study.

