[54,55] which calls into question the use of systemic neoadjuvant chemotherapy for this histologic type. Surgery remains the undisputed lynchpin of the curative treatment of gastric adenocarcinoma (subtotal or total gastrectomy with D2 lymph node dissection without splenectomy and pancreatectomy), but if systemic perioperative chemotherapy is to be recommended in Europe, the choice of perioperative treatment should be discussed on a case-by-case basis at Multi-Disciplinary Team meetings in order to take into account the patient’s pre and post-surgery general and nutritional state of health, the histology, and the preoperative and pathologic staging. Free intraperitoneal cancer cells originating from the primary tumor which invade the serosa prior to resection contribute to the peritoneal recurrence of resectable stomach cancer. Free cancer cells in the peritoneal cavity may also originate from the blood or the lymph which transport tumor cells to the surgical site. These cells may also originate from lymph node metastatis. Indeed, the surgical trauma resulting from the excision of the primary tumor provokes the release of tumor emboli in the peritoneal cavity which rapidly adhere the surface revealed by the removal of the tumor. Immediately after the intervention the resection site and traumatized peritoneal surfaces become covered in a fibrinous exudate which entraps tumor cells and protects them from the body’s defense mechanisms. This whole process constitutes the theory of what Paul Sugarbaker has called “tumor cell entrapment”
[56]. This is a key phenomenon which needs to be understood in order to fully comprehend the pathogenesis of recurrence, both at the site of resection and on the peritoneal surfaces, and to assess the beneficial effects of adjuvant perioperative intraperitoneal chemotherapy.

The increased incidence of postoperative positive peritoneal cytology has only been suggested in small Asian studies
[21,57]. Whilst the prognostic value of positive peritoneal cytology prior to resection seems to be well established
[20,58], the same cannot be said for post-resection peritoneal cytology whose prognostic value remains controversial but which may represent a key prognostic factor for peritoneal and locoregional recurrence.

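### Peritoneal cytology and clinical nodal status are collected before randomisation, but no stated efficacy analysis adjusts for them: a forgone gain in power, not a shortfall

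*Protocol article*

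**What the plan says.** All references are to the protocol article.

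- **Efficacy analysis** (Sample size calculation and statistical considerations). Overall survival is described by Kaplan-Meier curves and compared by a logrank test, with no strata or covariates mentioned. Then: "This analysis will then be confirmed using a Cox regression analysis taking into account the center effect (frailty Cox model"). No other covariate is named.
- **Prognostic standing of the factors.** The Discussion says "Whilst the prognostic value of positive peritoneal cytology prior to resection seems to be well established". The Peritoneal recurrence section begins its list with "Several factors favorable to peritoneal recurrence have been identified: invasion of the serosa (T3, T4 tumors") and goes on to free cancer cells in the washing, nodal invasion and signet ring cells. It calls peritoneal recurrence the main cause of failure after curative surgery.
- **When they are known.** Main inclusion criteria takes serosal and nodal status from endoscopic ultrasound and CT, and offers as a further entry route "and/or positive peritoneal cytology (sampled during the preoperative laparoscopy"). Pre-therapeutic work-up adds: "Staging videolaparoscopy of the abdominal cavity and peritoneal cytology testing will be carried out following the same procedure as during gastrectomy". The Abstract places randomisation at the end of curative surgery, so all of this comes earlier.
- **Stratification** (Randomization): centre and signet ring cells only.
- **Ancillary study.** Cytology is related to overall survival in a Cox model, but only as an exploratory analysis outside the treatment comparison.

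**The concern.** The entry routes are alternatives, so the trial mixes cytology-positive with cytology-negative patients and node-positive with node-negative patients. Randomisation does not balance these factors by design. If they predict death, a survival model that omits them estimates a hazard ratio closer to 1 than the one conditional on them, and has less power for the same number of deaths. A chance imbalance, for example more cytology-positive patients in one arm, would also go uncorrected in every stated efficacy analysis.

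With about 190 deaths expected and power planned at 80%, a few points matter, and the data are being collected anyway.

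**Working it through.** **1. The plan's own figure.** Inputs from Sample size calculation and statistical considerations: "5-year overall survival in the control group of about 30"%; "5-year overall survival in the intervention group of about 45% (i.e. an HR of 0.67"); "a maximum follow-up time of 5 years; an alpha of 5%, two-sided"; 80% power; 306 patients. Allocation is 1:1 (Protocol overview).

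- Hazard ratio: ln 0.45 / ln 0.30 = 0.663.
- Mean probability of death by 5 years: (0.70 + 0.55)/2 = 0.625.
- Freedman deaths: (1.960 + 0.842)² × [(1 + 0.663)/(1 − 0.663)]² ≈ 191.4.
- Patients: 191.4/0.625 ≈ 306.3. The stated 306 is reproduced.
- Expected deaths at 306: 306 × 0.625 ≈ 191. Power is 80.0% (Freedman) or 81.0% (Schoenfeld).

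**2. What adjustment would add.** The article gives neither prevalence nor hazard ratio for cytology (C), nodal status (N) or serosal invasion (S), so every value below is an assumption. Each row is 10,000 simulated trials of 306 patients with exponential survival given the factors and censoring at 5 years. The baseline hazard and conditional treatment effect were set so that overall five-year survival stays at 30% and 45%. The unadjusted logrank test is compared with the Wald test for arm in a Cox model that includes the factors. Centre and signet ring cells were not simulated. The Monte Carlo standard error of each power figure is about √(0.81 × 0.19/10,000) = 0.4 points.

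| Assumed prevalence and HR | Unadjusted | Adjusted | Gain (points) |
|---|---|---|---|
| Factors not prognostic | 81.0% | 80.7% | −0.3 |
| C 15%, 1.5; N 60%, 1.3; S 70%, 1.3 | 81.3% | 82.5% | +1.2 |
| C 10%, 2; N 60%, 1.5; S 80%, 1.3 | 81.3% | 83.7% | +2.5 |
| C 15%, 2; N 60%, 1.5; S 70%, 1.5 | 81.5% | 85.5% | +4.0 |
| C 20%, 2.5; N 60%, 2; S 70%, 1.5 | 82.1% | 89.6% | +7.5 |
| C 20%, 2.5; N 60%, 2; S 60%, 2 | 82.5% | 91.3% | +8.8 |
| C 20%, 3; N 50%, 2.5; S 60%, 2 | 83.9% | 94.5% | +10.6 |

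(Gains were computed before rounding.)

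**3. Closer to the entry rules.** The Peritoneal recurrence section equates serosal invasion with T3/T4, and Main inclusion criteria admits only T3 or T4, so S may hardly vary. The factors are also alternative entry routes, and N and S are clinical, hence imperfect, stages.

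| Variation | Unadjusted | Adjusted | Gain (points) |
|---|---|---|---|
| S constant; C 10%, 2; N 60%, 1.5 | 81.5% | 83.5% | +2.0 |
| S constant; C 15%, 2.5; N 60%, 2 | 81.8% | 88.5% | +6.7 |
| S constant; C 20%, 3; N 50%, 2.5 | 83.0% | 92.4% | +9.4 |
| At least one factor at entry; C 15%, 2; N 60%, 1.5; S 70%, 1.5 | 81.7% | 84.9% | +3.2 |
| The same, N and S staging 75% accurate | 80.8% | 82.8% | +2.0 |
| At least one factor at entry; C 20%, 2.5; N 60%, 2; S 60%, 2 | 81.7% | 88.4% | +6.7 |
| The same, N and S staging 75% accurate | 82.4% | 85.6% | +3.2 |

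**4. Further checks** (a separate simulation, 4,000 to 5,000 trials per scenario). Adjusting for cytology alone gave +1.4 points (10% positive, HR 2), +3.1 (10%, HR 3) and +5.0 (20%, HR 2.5). With no treatment effect, the rejection rate was 5.0% adjusted and 5.4% unadjusted.

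**The case against.** An unadjusted logrank test is a valid primary test, and the sample size is right for it. A reader might infer from the missing covariates that the trial is underpowered or the analysis wrong. The documents do not support that: 306 patients give the stated 80%.

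A reader might also want to fix the loss at one figure. That cannot be done, because no prevalence or effect size is given. Nor does the article call all three factors prognostic for survival. It says so explicitly only of pre-resection cytology; nodal and serosal invasion are listed as factors for peritoneal recurrence. The Abstract puts five-year survival of T3 and/or node-positive patients below 30%, but offers no contrast within the eligible population. Surgical technique also expects that preoperative chemotherapy may downstage tumours, which would weaken stages taken at the initial work-up. All this stands, and it pushes the likely gain towards the lower part of the range.

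Chance imbalance does not invalidate the test, since its type I error already allows for it. Part of the shift in the hazard ratio is a difference between marginal and conditional quantities, not bias. Both points stand. They leave the power gain intact, and adjustment still corrects the estimate for an imbalance that has actually occurred.

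Finally, a covariate list may sit in the full protocol or the analysis plan, neither of which is shown. That is possible, and it is why this is not put as an omission. The article does, however, state the efficacy model and the adjustment in it, and the point concerns that stated choice.

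**Conclusion.** The point holds as a worthwhile, low-cost improvement, not as an error. The stated efficacy analyses leave out two baseline factors that the trial collects and itself considers important.

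The forgone gain is about 1 to 3 points of power if effects are weak or clinical staging is misclassified, and about 2 to 9 points if effects are moderate to strong. It reached 10.6 points only when all three factors varied freely and were very strong. With serosal invasion constant, cytology and nodal status still gave 2.0 to 9.4 points. If the factors turned out not to matter, adjustment cost about 0.3 points, which is within simulation error.

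The direction is secure if the factors predict death. The size rests wholly on assumed prevalences and hazard ratios, on exponential survival, and on simulations without centre or signet-ring effects.

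**What to change.** In Sample size calculation and statistical considerations, prespecify that the planned centre-frailty Cox model also includes these fixed covariates:

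- peritoneal cytology at the staging laparoscopy (positive, negative, missing);
- clinical nodal status from the pre-randomisation work-up;
- signet ring cells, because randomisation is stratified on them;
- clinical serosal invasion, only if it varies among the patients entered.

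Report the adjusted hazard ratio from this model as the main effect estimate. Keep the logrank test as the primary test unless the sponsor changes it by a formal amendment before any outcome data by arm are seen; the trial is open, so a later switch could look data-driven. While the logrank test stays primary, the gain in power belongs to the Cox result only. The 306 patients and the stated 80% need no change.

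The cost is a short addition to the analysis text, with no new patients, visits or measurements. The hazard ratio becomes conditional on these factors, and a few degrees of freedom are spent against about 190 deaths.
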